### Outcomes

The primary outcome measures for the cross-sectional part of the study are **hippocampal volume**, the amount of cerebral hyperphosphorylated **tau** in neurofibrillary tangles, and **synaptic density** (SV2A glycoprotein) as determined by SUVR values derived from uptake of the PET tracers 18F-MK-6420 and 11C-UCB-J respectively. The primary outcome measures for the longitudinal part of the study are **change in hippocampal volume, tau and synaptic density following ECT** as determined by a baseline measurement prior to ECT and a second measurement after 10 ECT sessions. A fixed number of sessions was chosen to reduce bias due to differences in treatment duration whilst ensuring adequate clinical response within the study population. The relationship between the primary and other outcome measures and the study objectives are outlined in Table 1. This study will additionally generate numerous outcome variables that can be used to address secondary hypotheses relating, but not limited to, the objectives in this study.

**Table 1 Tab1:** Research questions and outcome data to be used to address the study objectives

Objective	Research Question	Experimental data	Variables
1	Hippocampal atrophy associated with SD?	**MRI: 3D T1** BRAVO & **3D T2** (morphometry & PET pre-processing) **PET:** ^**11**^**C-UCB-J PET** (SV2a: SD)	Hippocampal volume ^11^C-UCB-J SUVR
2	Tau associated with SD in hippocampus?	**MRI: 3D T1 BRAVO** & **3D T2** (as above) **PET:** ^**18**^**F-MK-6240** (tau)	Hippocampal volume ^18^F-MK-6240 SUVR
3	ECT-induced ΔGM in hippocampus associated with ΔSD?	**MRI: 3D T1 & 3D T2** (as above + post ECT) **PET:** ^**11**^**C-UCB-J PET** (SD)	Δ Hippocampal volume Δ^11^C-UCB-J
4	Tau associated with MTL WM damage?	**MRI: 3D FLAIR** (to define + quantify WML) **SWI & ASL** (perfusion/vascular pathology) **multi-shell diffusion** (DKI, NODDI + tractography) **PET:** ^**18**^**F-MK-6240** (tau)	Total + regional cerebral WML volume ^18^F-MK-6240 SUVR WM microstructural damage (e.g. MK, FA, ND), MTL WM fibre bundles
5	Pathological brain ageing mediated by CV risk factors?	**MRI: 3D T1 & T2** (as above) **MRI: 3D FLAIR** (to define + quantify WML) **SWI & ASL** (perfusion/vascular pathology) **PET:** ^**11**^**C-UCB-J PET** (SD) **PET:** ^**18**^**F-MK-6240** (tau) **Doppler ultrasound** (carotid artery) **Blood biomarkers** (lipids, glucose)	GM volume/cortical thickness Total + regional cerebral WML volume ^11^C-UCB-J & ^18^F-MK-6240 SUVR Intima-media thickness Serum lipids (HDL, LDL), glucose (HbA1c) Motor function metrics
6	Stress ➔ ↑tau & ↓SD ➔ MTL functional connectivity?	**MRI: resting-state fMRI** (fc connectivity) **3D T1** *(as above)* **PET:** ^**11**^**C-UCB-J PET** (SD) **PET:** ^**18**^**F-MK-6240** (tau) **Stress measures/EMA**	Hippocampal +amygdala volume ^11^C-UCB-J & ^18^F-MK-6240 SUVR fc in MTL associated resting-state networks physiological stress metrics / EMA response

Abbreviations: *SD* synaptic density, *ECT* electroconvulsive therapy; *GM* Grey matter, *MRI* magnetic resonance imaging, *SUVR* Specific uptake value ratio, *MTL* Medial temporal lobe, *WM* White matter, *WML* WM lesion, *SWI* susceptibility weighted imaging, *ASL* arterial spin labelling, *PET* positron emission tomography, *MK* mean kurtosis, *FA* fractional anisotropy, *ND* neurite density, *HDL* high density lipoprotein, *LDL* low density lipoprotein, *EMA* ecological momentary assessment, *HbA1c* haemoglobin A1c

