**Methods:**

This is a monocentric, clinical cohort study with a cross-sectional arm evaluating PET-MR imaging and behavioural measures in 64 patients with LLD compared to 64 healthy controls, and a longitudinal arm evaluating the same imaging and behavioural measures after 10 ECT sessions in 20 patients receiving ECT as part of their normal clinical management. Triple tracer PET-MRI data will be used to measure: hippocampal volume (high resolution MRI), synaptic density using [^11^C]UCB-J, which targets the Synaptic Vesicle Glycoprotein 2A receptor, tau pathology using [^18^F]MK-6240, and cerebral amyloid using [^18^F]-Flutemetamol, which targets beta-amyloid neuritic plaques in the brain. Additional MRI measures and ultrasound will assess cerebral vascular structure and brain connectivity. Formal clinical and neuropsychological assessments will be conducted alongside experience sampling and physiological monitoring to assess mood, stress, cognition and psychomotor function.

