Suspected non-amyloid pathology (SNAP) is a biomarker-based concept that applies to individuals with normal levels of amyloid-β in the brain, but in whom other biomarkers of neurodegeneration are present [9]. Tau protein is abundant in neurons and plays an important role in promoting microtubule assembly and stabilizing microtubule networks. Pathological hyperphosphorylation of tau renders it insoluble and leads to its aggregation in neuronal soma and as neurofibrillary tangles. Whilst tauopathy plays a central role in AD, medial temporal tau pathology is also considered as the most important constituent of SNAP [9]. Intriguingly, depressive symptoms have recently been related to tau accumulation [10]. Moreover, animal studies suggest that stress, an important depression risk factor, may be synaptotoxic through hyperphosphorylated tau accumulation in the synapse [11]. Following the development of the next generation tau tracer [^18^F]MK-6240 which targets tau associated with neurofibrillary tangles [12] and [^11^C]UCB-J, which targets the Synaptic Vesicle Glycoprotein 2A receptor to estimate synaptic density [13], it is now possible to investigate the relationships between SNAP, primary age related tauopathy (PART) [14] and stress in LLD.

One therapeutic intervention that has a profound effect on medial temporal lobe structure in LLD is electroconvulsive therapy (ECT). ECT is a safe, rapid-acting antidepressant therapy that has repeatedly been shown to induce a transient increase in hippocampal volume [15, 16]. However, the exact origin of these structural changes and their implications for the dramatic clinical improvement (and transient cognitive side-effects) associated with ECT remains unknown. Based on preclinical research, the leading hypothesis is that volumetric changes reflect changes in synaptic plasticity [17]. For example, repeated electroconvulsive seizures increase the total number of synapses in adult male rat hippocampus [18] and increased expression of the synaptic plasticity proteins neural cell adhesion molecule 1 (NCAM1) and the presynaptic protein synapsin 1 (SYN1) have been reported in hippocampus and prefrontal cortex [19]. The translation of these preclinical findings to patients being treated with ECT is critical for understanding its mechanism of action, yet prior to the availability of [^11^C]UCB-J it was not possible to measure synaptic density in humans in vivo.

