## Methods: Design

### Study aims and objectives

This study aims to shed light on how non-amyloid pathology may contribute to LLD pathology, identify the origin of LLD associated medial temporal lobe atrophy, and relate PET-MR imaging biomarkers to therapeutic response to ECT. Additionally, it aims to investigate the link between stress and MTL pathology. In order to achieve these aims, a number of objectives and associated hypotheses are proposed.

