### Interventions

In a subgroup of patients selected according to the clinical need for ECT (estimated *n* = 20, based on experience with earlier studies, see power analysis), ECT will be administered twice a week with a constant-current brief-pulse device (Thymatron System IV, Somatics, IL, USA). Anaesthesia will be achieved with intravenous administration of etomidate (0.2 mg/kg) and succinylcholine (1 mg/kg). Motor and EEG seizure will be monitored to ensure adequate duration and quality. Subjects will all be treated with right unilateral (RUL) ECT with stimulus intensity 6 times the initial seizure threshold (ST), as determined by empirical dose titration at the first treatment, until remission (Montgomery-Åsberg Depression Rating Scale (MADRS) < 10 in two consecutive ratings with a week interval). Subjects who failed to respond to RUL ECT after the sixth treatment will be switched to bitemporal ECT (1.5xST) (Dutch Guidelines for ECT [20]). The clinical criteria/indications for ECT are determined by the treating psychiatrist and include acute suicidality with high risk of acting out suicidal thoughts, psychotic features, rapidly deteriorating physical status due to complications from the depression (e.g. poor oral intake), history of poor response to medications, history of good response to ECT, patient preference, when the risks of standard antidepressant treatment outweigh the risks of ECT, particularly in medically frail or elderly patients, and catatonia.

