**Fig. 1 Fig1:**
[figure not shown]
Schematic timeline for L3D data collection. Figure legend: amy: Amyloid PET, blood: blood sampling (apolipoprotein □4 genotyping, blood glucose and serum lipids), CB: Chill Band wristband monitoring, CON: control subject, ECT: electroconvulsive therapy, EMA: ecological momentary assessment, LLD: late-life depression, MRI: magnetic resonance imaging, motor: neurological and task based assessment of motor function, NP: neuropsychological testing and psychiatric intake, SV2A: synaptic density PET with synaptic vesicle 2A tracer, t:tau PET, US: doppler ultrasound (intima media thickness) *following the 10th ECT treatment

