### Sample size

Our proposed sample size of 128 participants is based on the following calculations. As our hypotheses assume baseline group differences between controls and patients in hippocampal volume and synaptic density, and increases in hippocampal volume following ECT, we have based our power calculations on t-tests to determine such differences, rather than on correlations.

(1) Based on the results of our previous study [7] (Group 1 mean = 6396.251 mm^3^, Group 2 Mean = 6724.461 mm^3^, Group 1 Standard Deviation = 711.49 mm^3^ Group 2 Standard Deviation = 763.866 mm^3^), using the STATA statistical package POWER procedure, to have a power of at least 0.80 (0.804) to detect a group mean difference in normalized total hippocampal volume using a two-sample t-test with α-level of 0.05 (one-tailed), assuming a balanced design with equal group sizes, requires 64 subjects per group, i.e. 128 subjects in total.

(2) To examine hippocampal volume changes after ECT treatment we will assess normalized total hippocampal volume on a random sample of patients before and after the last ECT treatment. Based on the expected mean difference in normalized total hippocampal volume (− 188.333 mm^3^), pre 792.5462 mm^3^ and post standard deviations 864.075 mm^3^, and the correlation between pre and post volume hippocampal measurements (0.92908) from our previous study [15], to achieve 80% power (0.814) at an α-level of 0.05 (one-tailed) requires 20 subjects.

(3) Based on the results of a recent study [21] investigating differences in ^11^C-UCB-J binding in older healthy controls and AD patients with mild cognitive impairment and mild dementia (mean age = 73 years), (Group 1 mean = 0.87, Group 2 Mean = 1.47, Group 1 Standard Deviation = 0.5 Group 2 Standard Deviation = 0.37), to have a power of at least 0.80 (0.826) to detect a group mean difference in ^11^C-UCB-J (synaptic density) using a two-sample t-test with α-level of 0.05 (one-tailed), assuming a balanced design with equal group sizes, requires 8 subjects per group, i.e. 16 subjects in total.

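### The post-ECT scan is fixed after session 10 while ECT runs only until remission, so a patient who stops earlier has no defined second measurement

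*Protocol article*

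**What the plan says.** Three places in the protocol article agree on when the second longitudinal measurement is taken. Outcomes specifies "a baseline measurement prior to ECT and a second measurement after 10 ECT sessions". The Methods paragraph of the Abstract says "after 10 ECT sessions in 20 patients receiving ECT as part of their normal clinical management". The Fig. 1 legend places it "following the 10th ECT treatment". Outcomes also gives a reason: "A fixed number of sessions was chosen to reduce bias due to differences in treatment duration".

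Interventions sets the length of the ECT course in a different way. Treatment is given twice a week until remission, defined as a MADRS score of "< 10 in two consecutive ratings with a week interval". No minimum or maximum number of sessions is stated.

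Item (2) of Sample size, which justifies the 20 ECT patients, says that hippocampal volume will be assessed "before and after the last ECT treatment".

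Statistical analysis has a general provision for missing data that names direct likelihood and multiple imputation. The Discussion expects some incomplete datasets. Neither says when, or whether, a patient who finishes ECT before session 10 is scanned again.

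**The concern.** The time point in Outcomes and the time point in Sample size coincide only for a patient whose course ends at exactly session 10. Someone who remits and stops earlier never reaches the point at which the second measurement is defined. Someone who continues longer has a clearly defined scan, but not at the point that Sample size describes.

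The early stoppers matter more, because they would go unscanned for having responded quickly. Three things are affected:

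- the primary longitudinal outcomes (change in volume, tau and synaptic density);
- Objective 3, which needs both scans in the same patient;
- the stated aim to "relate PET-MR imaging biomarkers to therapeutic response to ECT", which would lose the fastest responders.

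A missing-data model can use the baseline scan and the MADRS ratings of such patients. It cannot supply a scan that was not taken.

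**Working it through.** **1. Can remission come before session 10?** Interventions gives two sessions a week, so 10 sessions take 10 / 2 = 5 weeks. Remission needs two qualifying ratings one week apart. The article does not give the full rating schedule. If ratings are weekly from the start (an assumption):

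- the earliest possible stop is after qualifying ratings at the ends of weeks 1 and 2, at about session 2 × 2 = 4;
- a first qualifying rating in week 3, confirmed in week 4, ends treatment at about session 2 × 4 = 8.

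The rule therefore allows a stop before the scan. This shows that it can happen, not how often.

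**2. Do the passages resolve the case?** The sentence in Outcomes on a fixed number of sessions can be read in two ways. If it fixes only the scan time, early remitters have no defined scan. If it fixes the length of the course, it contradicts treatment until remission in Interventions. Neither reading settles the matter.

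**3. The plan's own power figure.** The inputs are from Sample size, item (2): mean change 188.333 mm³ (absolute value), SD before 792.5462 mm³, SD after 864.075 mm³, correlation 0.92908, one-tailed α 0.05.

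SD of change = √(792.5462² + 864.075² − 2 × 0.92908 × 792.5462 × 864.075) = √(628,129 + 746,626 − 1,272,504) = √102,251 = 319.8 mm³.

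Standardised change = 188.333 / 319.8 = 0.589.

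Power of the paired t-test comes from the noncentral t distribution with n − 1 degrees of freedom and noncentrality 0.589 × √n:

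| Complete pairs | Noncentrality | Power |
|---|---|---|
| 20 | 2.63 | 0.814 |
| 19 | 2.57 | 0.795 |
| 18 | 2.50 | 0.774 |
| 16 | 2.36 | 0.727 |

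The stated 0.814 is reproduced, and 20 is the smallest n that reaches 0.80. Interventions expects about 20 ECT patients, so expected and required numbers are equal. The rows below 20 assume that the effect and SD are unchanged and that only complete pairs are analysed.

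**4. Bias in mean change.** Losing the quickest remitters shifts the mean change among the remaining patients only if imaging change is related to speed of remission. The Background says of the structural changes that "their implications for the dramatic clinical improvement (and transient cognitive side-effects) associated with ECT remains unknown". With no relation there is no shift. With a relation, the shift depends on its sign, its strength and the number lost. The article gives none of these, so no figure is derived here.

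**The case against.** The strongest reply is that this is a condensed article, and that scheduling the follow-up scan of someone who ends ECT early is visit-level detail for the full protocol. The article does not say that such patients go unscanned or are excluded. This stands in part: a reader might infer that the plan drops early responders, and the text does not support that. It is silent on them. But the timing of a primary outcome is stated in three places and described differently in a fourth, and that conflict is in the text itself.

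The fixed session number is also a reasoned choice. Scanning early stoppers after their last session brings back some of the variation in treatment duration that the sponsor wanted to avoid. This stands, and it is why the choice of primary analysis set is left to the sponsor below. It does not argue against taking the scan.

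No early-stopping rate is given, and the planned missing-data methods soften the effect of any loss. Both points stand and limit the size of the finding. Going from 0.814 to 0.795 is a small change, and the same would follow from attrition of any cause. The power figures also concern mean volume change; the effect on the association in Objective 3 is not quantified.

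Patients treated beyond session 10 lose nothing. For them only the wording in Sample size needs attention.

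**Conclusion.** The inconsistency is real and should be fixed. Followed as written, the rules leave a patient who remits and stops before session 10 without the second measurement that defines the primary longitudinal outcomes, and this loss depends on response. Sample size names a different time point from the other three places.

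The size is uncertain and may be small. It depends on how many patients stop before about 5 weeks, which the article does not state. The power calculation is arithmetically correct. What it lacks is reserve, since a single lost pair takes it just below 0.80.

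A reader might infer that the mean volume increase would be understated by some definite percentage. The documents do not support this. Any such figure would rest wholly on an assumed number lost, an assumed correlation and an assumed sign, and neither the direction nor the size of a bias is known.

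**What to change.** - **Outcomes:** state that the second measurement is taken after the 10th session, or after the final session if ECT ends earlier. Timing is unchanged for everyone who reaches session 10.
- **Sample size, item (2):** replace the reference to the last treatment with the same rule.
- **Data collection:** record the number of sessions received and the interval from the last session to the scan.
- **Analysis:** report results for all scanned patients and for those scanned after 10 sessions, and name in advance which is primary. The restricted set keeps treatment duration constant but again leaves out early remitters; the full set does the reverse.

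The cost is two short text edits, two recorded items and one further analysis. There are two drawbacks. Session number will vary with response among early stoppers. Their post-ECT scan dates must also follow their last session, which adds to the tracer and scanner coordination that the Discussion already describes as demanding. The rule should be settled early, because a scan missed at the end of a course cannot be recovered.

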### Participant timeline

Data will be collected from participants during four visits for the cross-sectional part of the study, and eight visits for the longitudinal part (ECT group). The first visit will comprise the intake, obtaining informed consent, clinical neurological, psychiatric and neuropsychological assessments, and venous blood sampling for genotyping, glycated hemoglobin (HbA1c) and serum lipid measurements. At the end of the first visit, the participants also receive the Chill Band (a wristband monitoring device) and a dedicated smartphone for ecological momentary assessment (EMA). PET-MR imaging will be conducted at the second, third and fourth visit. Cerebrovascular ultrasound will also be performed during one of these visits (Fig. 1).

**Fig. 1 Fig1:**
[figure not shown]
Schematic timeline for L3D data collection. Figure legend: amy: Amyloid PET, blood: blood sampling (apolipoprotein □4 genotyping, blood glucose and serum lipids), CB: Chill Band wristband monitoring, CON: control subject, ECT: electroconvulsive therapy, EMA: ecological momentary assessment, LLD: late-life depression, MRI: magnetic resonance imaging, motor: neurological and task based assessment of motor function, NP: neuropsychological testing and psychiatric intake, SV2A: synaptic density PET with synaptic vesicle 2A tracer, t:tau PET, US: doppler ultrasound (intima media thickness) *following the 10th ECT treatment

### Sample size

Our proposed sample size of 128 participants is based on the following calculations. As our hypotheses assume baseline group differences between controls and patients in hippocampal volume and synaptic density, and increases in hippocampal volume following ECT, we have based our power calculations on t-tests to determine such differences, rather than on correlations.

(1) Based on the results of our previous study [7] (Group 1 mean = 6396.251 mm^3^, Group 2 Mean = 6724.461 mm^3^, Group 1 Standard Deviation = 711.49 mm^3^ Group 2 Standard Deviation = 763.866 mm^3^), using the STATA statistical package POWER procedure, to have a power of at least 0.80 (0.804) to detect a group mean difference in normalized total hippocampal volume using a two-sample t-test with α-level of 0.05 (one-tailed), assuming a balanced design with equal group sizes, requires 64 subjects per group, i.e. 128 subjects in total.

(2) To examine hippocampal volume changes after ECT treatment we will assess normalized total hippocampal volume on a random sample of patients before and after the last ECT treatment. Based on the expected mean difference in normalized total hippocampal volume (− 188.333 mm^3^), pre 792.5462 mm^3^ and post standard deviations 864.075 mm^3^, and the correlation between pre and post volume hippocampal measurements (0.92908) from our previous study [15], to achieve 80% power (0.814) at an α-level of 0.05 (one-tailed) requires 20 subjects.

(3) Based on the results of a recent study [21] investigating differences in ^11^C-UCB-J binding in older healthy controls and AD patients with mild cognitive impairment and mild dementia (mean age = 73 years), (Group 1 mean = 0.87, Group 2 Mean = 1.47, Group 1 Standard Deviation = 0.5 Group 2 Standard Deviation = 0.37), to have a power of at least 0.80 (0.826) to detect a group mean difference in ^11^C-UCB-J (synaptic density) using a two-sample t-test with α-level of 0.05 (one-tailed), assuming a balanced design with equal group sizes, requires 8 subjects per group, i.e. 16 subjects in total.

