### Primary objectives

#### Objective 1

To examine whether lower hippocampal volume in LLD is associated with decreased synaptic density. *Hypothesis: Hippocampal volume will be positively correlated with synaptic density* i.e. *a lower hippocampal volume will be associated with a lower accumulation of MTL [*^*11*^*C]UCB-J.*

#### Objective 2

To study the relationship between medial temporal synaptic density and tau accumulation in LLD. *Hypothesis: Hippocampal volume will be negatively correlated with tau accumulation* i.e. *a lower hippocampal volume will be associated with a higher accumulation of MTL [*^*18*^*F]MK-6240.*

#### Objective 3

To examine whether hippocampal volume increase following ECT is associated with increased synaptic density. *Hypothesis: Hippocampal volume increase following ECT will be positively correlated with synaptic density* i.e. *Higher hippocampal volume will be associated with higher binding of MTL [*^*11*^*C]UCB-J following ECT.*

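### The patient-control differences that set the sample size are tied to no objective, hypothesis or Table 1 row, and the stated volume-PET regression has no group term

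*Protocol article*

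**What the plan says.** The Abstract presents the cross-sectional arm as "evaluating PET-MR imaging and behavioural measures in 64 patients with LLD compared to 64 healthy controls". The Sample size section gives its premise as "As our hypotheses assume baseline group differences between controls and patients in hippocampal volume and synaptic density", and continues: "we have based our power calculations on t-tests to determine such differences, rather than on correlations". The calculation that fixes the total uses normalized total hippocampal volume ("Group 1 mean = 6396.251 mm^3^, Group 2 Mean = 6724.461 mm^3"; "Group 1 Standard Deviation = 711.49 mm^3^ Group 2 Standard Deviation = 763.866 mm^3") and concludes, "using a two-sample t-test with α-level of 0.05 (one-tailed), assuming a balanced design with equal group sizes, requires 64 subjects per group".

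Objective 1 under Primary objectives reads: "To examine whether lower hippocampal volume in LLD is associated with decreased synaptic density". Its hypothesis is a positive correlation between volume and synaptic density. The matching Table 1 row asks "Hippocampal atrophy associated with SD" and lists two variables, hippocampal volume and 11C-UCB-J SUVR. The other objectives and rows likewise concern associations, mediation or change after ECT. None names a patient-control contrast or lists group as a variable.

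Under Statistical analysis, the volume-tau and volume-synaptic density questions are assigned a voxel-wise regression with age and total intracranial volume as covariates. Group is not mentioned there. The same section lists t-tests among the conventional methods for objectives 1 to 6. The Imaging section mentions voxel-based group differences.

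**The concern.** The sample size rationale credits the hypotheses with something they do not contain. Two different questions are in play: whether patients differ from controls in volume and synaptic density, and whether volume and synaptic density go together across people. The study is sized on the first, while the objectives state only the second.

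This affects what can be concluded. Objective 1 is worded around lower volume and decreased synaptic density in LLD, but its hypothesis tests neither against controls. A positive correlation could be a general feature of older brains. If patients and controls are pooled without a group term, it could also be produced by two separate group differences with no link between volume and synapses inside either group. In the other direction, a real patient-control deficit has no named objective under which to be reported.

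**Working it through.** **1. The plan's own figure.** Inputs are from the Sample size section. Difference = 6724.461 − 6396.251 = 328.21 mm³. Pooled SD = √[(711.49² + 763.866²)/2] = 738.14. So d = 328.21/738.14 = 0.445. With 64 per group, the noncentrality is 0.4446 × √32 = 2.515 on 126 degrees of freedom. One-tailed power at 0.05 is 0.804, as stated, and 64 is the smallest size that reaches 0.80. The arithmetic is sound for the contrast it addresses.

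**2. A correlation shared with controls.** Assume no group difference and the same correlation r in both groups. The article gives no r, so a range is shown. For a single-region, one-tailed test in the 64 patients without covariates, probability of a positive result ≈ Φ(atanh(r)·√61 − 1.645). At r = 0.3 this is Φ(0.3095 × 7.810 − 1.645) = Φ(0.772) = 0.78.

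| assumed r | formula | simulation |
|---|---|---|
| 0.2 | 0.48 | 0.48 |
| 0.3 | 0.78 | 0.79 |
| 0.4 | 0.95 | 0.95 |
| 0.5 | 0.996 | 0.996 |

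In the same setting the patient-control test is positive about 5% of the time.

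**3. A correlation created by pooling.** Assume no association within either group, and treat the lower-mean group as patients. Volume: d₁ = 0.4446. Synaptic density, from the third calculation in the Sample size section: d₂ = (1.47 − 0.87)/√[(0.5² + 0.37²)/2] = 0.6/0.4398 = 1.364. With equal groups, the correlation induced in the pooled sample is

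r = (d₁d₂/4) / √[(1 + d₁²/4)(1 + d₂²/4)] = 0.1516/√(1.0494 × 1.4652) = 0.122.

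Probability of a positive one-tailed test in 128 ≈ Φ(atanh(0.122)·√125 − 1.645) = Φ(1.374 − 1.645) = 0.39. Simulation gives 0.40 without a group term and 0.05 with one.

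The value of d₂ comes from a comparison of controls with Alzheimer's patients, so it may be too large for LLD:

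| assumed d₂ | induced r | positive, no group term | positive, group term |
|---|---|---|---|
| 1.364 | 0.122 | 0.40 | 0.05 |
| 1.0 | 0.097 | 0.29 | 0.05 |
| 0.445 | 0.047 | 0.13 | 0.05 |

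**4. What 64 per group can say about a difference in correlation.** One-sided power ≈ Φ([atanh(r₁) − atanh(r₂)]/√(2/59) − 1.645), where 59 = 64 − 3 − 2 covariates. Results: 0.4 against 0.2, 0.33; 0.5 against 0.3, 0.37; 0.5 against 0.2, 0.59; 0.6 against 0.3, 0.67. An interaction term is informative as an estimate but too weak to act as a gate.

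**The case against.** The strongest reply is that the group contrast is stated. The Sample size section gives variable, test, alpha and sidedness for both volume and 11C-UCB-J. The Abstract and the Imaging section mention group comparison, the controls are matched, the primary outcome measures are marker levels, and t-tests are listed for objectives 1 to 6. This stands. A reader might infer that no patient-control comparison is planned or that the controls have no purpose, and the article does not support either. What is missing is the link from that comparison to an objective.

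Second, Objective 1 can be read as a statement about individuals, with lower volume in LLD taken as a premise from the team's previous study. On that reading objective and hypothesis agree. This is fair. A reader might also infer that the article has a rule by which a significant correlation settles Objective 1. It has none. Nor do the two contrasts give opposite conclusions; they answer different questions.

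Third, the percentages in step 2 are power at an assumed true correlation, not error rates. That is correct. They show only that the hypothesis as written does not separate a patient-specific association from a general one. Step 3 is a false-positive rate for within-group association, but only if the data are pooled, which the article neither says nor excludes. Both steps concern one regional test, not a corrected voxel-wise map.

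Fourth, which participants enter the model is commonly left to a fuller document. That answers the model detail. It does not answer a sample size rationale that attributes to the hypotheses a contrast absent from all of them, when objectives and Table 1 are set out in the article.

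**Conclusion.** The point holds as a mismatch between the sample size basis and the stated objectives, with a consequence for interpretation. The sample size arithmetic is not at fault. As written, Hypothesis 1 can be met by a correlation common to controls (probability 0.48 to over 0.99 for an assumed r of 0.2 to 0.5 in 64 patients). If the groups are pooled without a group term, it can be met by group differences alone, in about 40% of trials at the article's own effect sizes and about 13% if the synaptic effect is only as large as the volume effect. These figures assume normal data, a single regional measure and a one-tailed 0.05 test. Requiring group differences before Objective 1 counts as supported would be stricter than the investigators' own claim and is not needed. It is enough that an LLD deficit is not inferred from the correlation.

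**What to change.** 1. Name the LLD-control difference in normalized total hippocampal volume, and in 11C-UCB-J SUVR in the primary region, as explicit objectives with their own Table 1 rows. The present 64 per group already covers the volume contrast as specified.
2. Add group and group-by-synaptic density terms to the regression, and report the association with its interval in patients and in controls. Treat the interaction as an estimate, not a pass/fail criterion. With power of about 0.33 to 0.67 for correlation gaps of 0.2 to 0.3, a non-significant interaction would not show that the association is the same in both groups.
3. Describe an LLD deficit in volume or synaptic density only where the group contrast shows it.

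The cost is some rewording, a few more analyses of data already being collected, and a more limited Objective 1 conclusion. Recruitment and imaging do not change.
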